### Fidelity patient sample

Participants in the fidelity study will include both UAIHC patients and members of the UAIHC clinic team. On fidelity assessment sample days (a single randomly chosen day of the last week of the data collection month; see data collection procedures below), participants will be recruited and enrolled from all patients who enter the UAIHC waiting room. It is anticipated that approximately 180 patients will consent to participation across the two-year study period. The inclusion/exclusion criteria for this sample are identical to those used for the outcomes sample with the exception that patients who are currently pregnant will be allowed to participate in this sample.

At check in on the fidelity data collection day, front desk staff will make a printed handout available describing a “How is UAIHC Doing?” evaluation, and asking all patients seen that day to provide feedback through an online questionnaire after that day’s visit. Interested patients will supply their e-mail address and check a box on the printed handout expressing permission to receive the online questionnaire. The UA Study Coordinator will send all interested patients an e-mail with instructions and a link to the secure URL address for the fidelity informed consent form and the Web-based questionnaire. Patients preferring to complete the questionnaire on paper will have the opportunity to receive a hard copy from the front desk (or by mail) with instructions to place completed questionnaires in a secure box at the clinic (or to return them using the enclosed self-addressed stamped envelope). Digitally-signing the informed consent form, or returning a signed paper-based consent form will constitute completion of the informed consent process for fidelity. Patients who complete the questionnaire within 10 days will receive a $10 gift card.

### Fidelity clinic personnel sample

The UA Study Coordinator will enroll UAIHC personnel at study start by sending an e-mail with a link to the secure URL address and password information for the informed consent form. Assessments will be on the same schedule as for patient fidelity (see Data collection below). A total of 15–20 clinic personnel (the entire UAIHC staff) will be enrolled in the fidelity study. The same consent process and incentive will be used as for the fidelity patient sample.

### Qualitative/case study sample

The qualitative study sample will be a subset of the outcomes sample. In addition to the inclusion and exclusion criteria of the outcomes sample subjects will consist of members who joined the study during its first three months. The qualitative study will be introduced to patients by the UA Study Coordinator during the same meeting in which the outcomes study is discussed. Participation will require an additional consent, and will entail a 20–30 minute semi-structured, taped interview immediately following each regular outcome data collection points.

### Intervention

The IM professional practice model for primary care utilizes an inter-professional, physician-led, integrative clinical team to provide patient-centered care. UAIHC services include conventional medical care, lifestyle interventions, and evidence-based CM interventions. In particular, services include longer visits with providers, a commitment to health, a partnership agreement with the health care team, increased access via telephone and email in addition to in-person visits and classes, and a wider range of services including nutritional counseling, acupuncture, chiropractic care, stress-reducing mind-body approaches, and health coaching. In addition to individual appointments, group visits and health promotion classes are offered (e.g., nutrition, yoga, meditation). Emphasis is placed on motivating and supporting lifestyle behavior change. Although patients with a wide variety of diagnoses will be eligible and included in the study, outcomes for patients with the following five conditions (low back pain, fibromyalgia, other musculoskeletal conditions, metabolic syndrome and diabetes, and cardiovascular disease) will be analyzed separately where possible.

The UAIHC business model uses a hybrid financing approach that utilizes usual insurance reimbursements supplemented by a patient membership fee. The membership fee covers a certain number of CM practitioner visits, health coaching visits, and classes (a “class” may comprise a series of individual sessions). Three fee tiers have been established: 1) basic bundle (5 visits with the patient’s choice of CM practitioners, 2 visits with a health coach, and 2 groups or classes); 2) core (10 visits with the CM practitioners of choice, 4 health coach visits, and 4 groups or classes); and, 3) expanded (20 visits with CM practitioners, 8 visits with a health coach, and 8 groups or classes). For some members, this fee is partially offset by collaborating employers who offer UAIHC as an employee health benefit option. (Grant funding supports the costs of this study for those participants employed with these collaborators).

According to its business plan, the IM primary care practice model will follow IM principles [44] as well as the principles of primary care [45,46] and the patient-centered medical home [47]. More detail on the IM primary care practice model is presented in Dodds et al [48].

### Comparison group(s)

Data from UAIHC patients will be compared, where possible, to those of patients seen in other clinics. The primary outcome, total healthcare utilization, will be obtained from healthcare claims data for patients whose employers have given access to those data. For these patients, matched comparison groups will be developed using two different matching algorithms applied to de-identified claims data for non-UAIHC patients. One will use a straight matching algorithm based on age and gender, and the other will use propensity scores to match [49]. At least one of the participating employers also has employee lab values available. Where these data are available, the same matched comparison groups will be used to compare changes in key lab values seen across groups. Finally, several of the self-report measures have national and regional comparisons available. The measures of patient experiences and patient satisfaction are drawn from the Consumer Assessment of Healthcare Providers and Systems (CAHPS) Adult Visit Survey 2.0 [50]. The CAHPS website contains data on the results of these questions nationally, by region, and by physician specialty. The results seen for UAIHC participants will be compared to those seen by all providers nationally, by all providers in the West region, and by family practice doctors nationally. The measures of diet and exercise quality come from the Center for Disease Control and Prevention’s Behavioral Risk Factor Surveillance System survey [51]. National and statewide averages are available for these items. Unfortunately, no other secondary data sources are available for comparisons. For all other outcomes, UAIHC participants will act as their own controls by comparing their outcome measures over time to baseline.

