### Outcome measures

Data on clinical and economic outcomes will be collected from three main sources: self-report instruments, chart abstraction, and health plan administrative data (healthcare utilization and, where available, lab values) from participants’ employers. Because integrative medicine approaches treat the whole person, rather than simply targeting a specific disease or symptom, they can have broad impacts on health [25,29,35,36]. Therefore, a broad set of clinical and economic outcomes for the UAIHC will be captured (Table 1). These are each discussed below, starting with the self-report measures. All are collected at baseline (some directly and some as part of patients’ initial clinic intake form), and then 3, 6 and 12 months and semi-annually thereafter, unless otherwise noted.

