### Data collected from medical records

These data will be collected at 3, 6, and 12 months. A medical records abstraction form will be used to collect the following from the patient chart for the period since the last outcomes data collection point. The results of any of the following lab tests will be captured: fasting glucose, lipid panel, thyroid stimulating hormone (TSH), glycosylated hemoglobin (HbA1c), inflammatory markers (erythrocyte sedimentation rate and high-sensitivity C-reactive protein), vitamin D status, and measures of anemia (hemoglobin, hematocrit, and mean corpuscular volume). Also captured will be each patient’s diagnosis(es), systolic and diastolic blood pressure, heart and respiratory rates, weight, waist circumference, body fat composition, smoking status, and whether the patient is on hypoglycemic, dyslipidemia, or hypertension medication. Composite scores (10-year cardiovascular disease (CVD) event risk [70], 10-year CVD mortality risk [71], and metabolic syndrome diagnosis [72]) will be captured from the chart when recorded, or will be calculated. Forced vital capacity and forced expiratory volume will be captured for participants with pulmonary disease.

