### Health Insurance Claims Data

Annually, the UA Study Coordinator will create a coded, numeric list of study participants, who are employees or adult dependents of participating employer groups, to send to their health plan. This list will enable the health plan to generate and return a file of otherwise de-identified health claims data. Study participants will be identifiable (a partial waiver of protected health information data was granted by the UA Institutional Review Board) so that healthcare utilization data can be matched to their other study data, and the remainder of the file will be used to generate the matched control groups. The initial data request will cover one year prior and one year after clinic enrollment for study participants, and a comparable 2-year period for non-participants.

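### Lab changes are to be compared in the groups matched for cost, so balance is not assured among the members who actually have lab values

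*Protocol article*

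**What the plan says.** Under Comparison group(s), the protocol article describes "two different matching algorithms applied to de-identified claims data for non-UAIHC patients", made for the cost outcome: "One will use a straight matching algorithm based on age and gender, and the other will use propensity scores to match". The propensity covariates are not listed. On labs the same section says "At least one of the participating employers also has employee lab values available", and continues that, where such values exist, "the same matched comparison groups will be used to compare changes in key lab values seen across groups".

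Three other places bear on this. Health Insurance Claims Data describes the participants listed for the health plan as those "who are employees or adult dependents of participating employer groups", and the rest of the returned file supplies the controls. Outcome measures names the source of the employer labs as "health plan administrative data (healthcare utilization and, where available, lab values", separately from chart abstraction. Setting and Participants says that two employers currently contribute to the membership fee.

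**The concern.** The groups are built to be comparable for costs, over everyone with claims. The lab comparison can use only those with a result in both periods, and this subset may be limited to one employer and perhaps to its employees. No section says that the groups are re-formed or that balance is checked in that subset. Keeping the same groups means that a participant with labs may have a partner without them. Those who remain need not be alike in age, gender or propensity score, and still less in their starting lab value.

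This appears to be the only clinical measure set against a matched group. Table 1 gives medical records data a pre/post comparison only, and diet, exercise and satisfaction are set against published averages. A difference in lab change would be read as a matched result even if part of it reflected who happened to have lab values.

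**Working it through.** **The plan's own figure.** None is given for the lab comparison. The only sample size is 200 for total costs (Outcomes sample: d = 0.20, power 0.80, alpha 0.05). As a paired or one-sample calculation, ((1.960 + 0.842) / 0.20)² = 196.2, so 197, or 199 with the t distribution. The stated 200 is reproduced on that basis. It does not bear on labs and serves below only as a convenient starting count.

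**Step 1: pairs left intact.** All rates here are assumptions. Let e be the share of members at lab-holding employers, u the share of UAIHC members there with both values, and c the same share for comparison members.

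- Partners always from the same employer: 200 × e × u × c.
- Partners drawn without regard to employer: 200 × e² × u × c.

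| e | u | c | Same employer | Across employers |
|---|---|---|---|---|
| 1 | 0.9 | 0.9 | 162 | 162 |
| 1 | 0.9 | 0.5 | 90 | 90 |
| 1 | 0.9 | 0.3 | 54 | 54 |
| 0.5 | 0.9 | 0.9 | 81 | 40.5 |
| 0.5 | 0.9 | 0.5 | 45 | 22.5 |
| 0.5 | 0.9 | 0.3 | 27 | 13.5 |

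If labs cover employees but not dependents, u and c fall further. These counts show lost pairs, not bias.

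**Step 2: possible bias.** This was simulated with no treatment effect, a standardised lab value, a correlation of 0.7 between baseline and follow-up, and 400,000 people per side. About 90% of UAIHC members have values regardless of level. In comparison members, the log-odds of having values rises by s per SD of the baseline value.

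| s | Comparison members with values | Their mean baseline (SD) | Spurious difference in change, UAIHC minus comparison (SD) |
|---|---|---|---|
| 0 | 50% / 27% | 0.002 / 0.005 | 0.002 / 0.005 |
| 0.5 | 50% / 28% | 0.24 / 0.34 | 0.07 / 0.10 |
| 1.0 | 50% / 30% | 0.41 / 0.59 | 0.12 / 0.18 |

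The mechanism is regression to the mean. Expected change at baseline b is (0.7 − 1) × b = −0.3b, so the difference should be about 0.3 times the comparison group's excess baseline: 0.3 × 0.24 = 0.07 and 0.3 × 0.59 = 0.18, as simulated. Comparison members fall more, so for a lab where lower is better the error runs against UAIHC. For other labs or other testing patterns it could run the other way. With s = 0 only simulation noise remains.

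**Step 3: what adjustment does.** In this scenario expected follow-up at a given baseline is 0.7b in both groups. Comparing follow-up adjusted for the pre-period value therefore removes the spurious difference. It does not do so if having a follow-up value depends on later health or on clinic care.

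**The case against.** A reader might infer that the matching breaks and that tested comparison patients do differ from UAIHC patients. The documents do not establish this. They do not say why employer labs were drawn or what share of members have them. Broad workforce screening would give high coverage and little selection. These are risks, not facts.

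The opening words of "Where these data are available, the same matched comparison groups will be used to compare changes in key lab values seen across groups" can be read as confining the comparison to the lab-holding employer. Controls come from the remainder of the file returned by the participants' health plan, which fits same-plan matching, and the Analysis section gives age and gender only as examples. Cross-employer pairs are therefore possible but not stated. The Analysis section also describes differences between group means and specifies no pair-level lab analysis, so the loss of pairs matters mainly through balance and precision. All this stands. It narrows the concern but supplies neither two values per member nor balance among those who have them.

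A reader might also suspect that clinic-ordered chart results would fill gaps on the UAIHC side only. The documents do not support that. Data collected from medical records says "The results of any of the following lab tests will be captured", but Study design and Table 1 keep medical records data to comparison with baseline, and Outcome measures lists the employer labs as a separate source.

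Finally, a condensed article may leave balance checks and missing labs to a fuller document. That would answer silence, but here the article states which groups will be used. A plan that re-matched for labs would have to depart from that sentence.

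**Conclusion.** The point holds in a limited form. The protocol fixes the cost-matched groups as the comparison for lab changes, while lab values are assured for a narrower set of people than those groups were drawn from. Balance among members with both values is not assured, and selective testing could bias the result.

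The size cannot be taken from the documents. On the assumed coverage, 200 pairs leave between about 14 and 162 intact. The spurious difference runs from near zero, when having labs is unrelated to their level, to about 0.18 SD in the strongest scenario tried. That upper value is close to the d of 0.20 used to plan the cost outcome, although the two concern different outcomes.

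The lab comparison is secondary: it has no control-group mark in Table 1 and is not among the outcomes listed for the matched claims analysis. The primary cost comparison is untouched. The change is worth making because it is cheap and improves on the stated method.

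**What to change.** In Comparison group(s), replace the statement that "the same matched comparison groups will be used to compare changes in key lab values seen across groups" with the following rules for lab outcomes:

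- Form new comparison groups with the same two algorithms, within the employer(s) that hold lab data, among members with a pre-period value of the lab in question.
- Report balance between groups among those with both a pre and a post value.
- Adjust the comparison for the pre-period lab value.
- Report the share of each group with a follow-up value.

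The cost is an additional matching run for the lab outcomes and a few lines of text, with no new data collection. The lab comparison group will differ from the cost comparison group and will cover only members with lab data. Selection on follow-up testing is reduced or made visible, not removed, and if the two source populations differ in their stable level of a lab, adjustment for one baseline value may leave some bias. How many participants would be retained cannot be computed, because the size of the lab-holding pool is not given.

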### Data Collection

For the outcomes evaluation, data will be collected from patient charts and self-reports at four intervals—baseline (initial clinic visit), and at 3-, 6-, and 12-month follow up periods. Participants will receive a reminder email one week before each data collection due date. Baseline data will be due within one week of enrollment. In the email they will be directed to a secure website where they can access and complete the outcomes data collection instrument. If participants have not entered their data within 3 days of their due date, they will receive another reminder email, and those who have not entered their data within another 3 days of their due date will receive a call from the UA Study Coordinator. Healthcare utilization and cost data from healthcare claims will be obtained from their employer with study participant consent. These data will be collected for one year before and one year after clinic enrollment approximately 3 months after the 12-month follow up period to allow time for all incurred claims to be recorded. De-identified claims data for the comparison groups will be collected for the same period of time with “baseline” being defined by the average start date of study participants.

Because the intervention may change over time as clinic operations start up and mature [21], fidelity monitoring data will be collected monthly from study start for 6 months, then quarterly for 6 months, and then semi-annually. Patient-reported fidelity data will be gathered on a single randomly chosen day of the last week of the data collection month from all patients seen at the UAIHC clinic that day. This day will be selected by the UA research team using a simple computer generated randomization scheme and delivered to the UA Study Coordinator the week before the data collection week. A self-administered patient version of the “How is UAIHC doing?” questionnaire will be used for patients. For clinic personnel, fidelity data will be collected during the last week of each fidelity data collection month using an online self-administered practitioner and staff version of the “How is UAIHC doing?” questionnaire. Data from audits of randomly selected, de-identified patient charts and of administrative records will also be used to assess indicators of model implementation.

Qualitative data in the form of the results of 20–30 minute semi-structured interviews will be collected by phone or in-person approximately every three months, and at other significant points in time if the patient agrees—e.g., if the patient chooses to leave the clinic or there is a dramatic change in the patient’s use of clinic services. The focus is to collect real-time data on what the patient believes is the cause of any changes (or lack of change) seen in their health.

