### Outcomes sample

Only patients who are members at UAIHC and who meet the inclusion/exclusion criteria are eligible to enroll in this study. Participation in the study will continue for at least one year after enrollment. It is anticipated that at least 500 patients will consent to participation during the first nine months of the study. Our primary outcome for our main analysis is change in total costs (see the Analysis section below). Using the standard deviation seen in a set of healthcare utilization data from a related group, a sample size of 200 patients should be sufficient to detect a small effect size (Cohen’s d = .20) difference in total costs at a .80 power using an alpha of .05. Therefore, our expected sample size of 500 may also allow for some subgroup analysis. Inclusion criteria: 1) Enrollment in primary care (members) at UAIHC; and, 2) adults ages 18 or older. Exclusion criteria: 1) currently pregnant at time of recruitment; 2) patients who attend the UAIHC clinic as “consultation-only” patients; and, 3) significant cognitive impairment to the extent that the individual is unable to understand the consent and respond to questionnaires.

All new patients will be advised by their primary care physician that they may be eligible to participate in a study to evaluate the effectiveness of the UAHIC. Prior to checkout, patients have an exit session with the University of Arizona (UA) Study Coordinator. During this session (or if necessary, through a follow-up phone call), the Study Coordinator will explain the nature of the study and make a determination of study eligibility, and if appropriate, consent the patient. Patients who joined the UAIHC before study start (July 2013) will also have the opportunity to participate. The study will be explained at their first UAIHC visit after study start.

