The fifth analysis will focus on the subset of patients for which health insurance claims data are available and will utilize a matched comparison design. Prior to analysis all claims data for each individual (treatment and comparison groups) will be aggregated (by summation) into per health plan member per month (PMPM) totals of paid amounts (the amount paid by the health plan to the practitioner) for each of the following cost categories: total, inpatient, outpatient, emergency room, physician, and pharmaceutical claims. Similarly, the numbers of outpatient visits, hospital stays and emergency department visits will also be aggregated for each individual. The primary outcome will be total cost. Two comparison groups from de-identified claims data will be created—one using simple matching (e.g., by age and gender) and one using propensity scores [49]. After the comparison groups have been selected, simple descriptive analyses will show average PMPM costs and healthcare utilization (including standard deviations and other measures of dispersion) pre- and post- enrollment (or an equivalent date for the comparison groups) by gender, age, baseline diagnosis and by treatment and comparison group. Because cost data tends to be highly skewed, average PMPM costs and healthcare utilization pre/post enrollment, and the change in costs and utilization pre/post between the treatment and each of the comparison groups will be reported as mean differences with confidence intervals calculated using bootstrap methods [83,84]. Because of the number of data points for each patient (e.g., up to 12 PMPM values pre-enrollment and 12 post-enrollment), HLM [80-82] will be used to estimate the pattern of change in healthcare utilization and costs over time, and to explore the determinants of those patterns. Fidelity measures with significant changes over time [24], demographics, participants’ membership level and baseline diagnoses will be included as covariates in these models. Finally, changes in costs between groups will be compared to changes in patients’ CVD risk.

Results for the last two analyses will be reported following the Strengthening the Reporting of Observational Studies in Epidemiology (STROBE) guidelines [85]. For all outcomes, the estimated treatment effects will be reported using their original outcome scale and including confidence intervals.

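### All comparison members share one average index date while participants keep their own, and the pool as described can include clinic members: bias in the cost contrast is possible, not established

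*Protocol article*

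**What the plan says.** The claims windows are set in Data Collection. For participants, "These data will be collected for one year before and one year after clinic enrollment"; for the comparison groups, the same length of time is used, with baseline "being defined by the average start date of study participants". Two other sections touch on the comparators' dates, and neither replaces this rule with an individual date. Health Insurance Claims Data asks for "a comparable 2-year period for non-participants", and Analysis describes costs "pre- and post- enrollment (or an equivalent date for the comparison groups".

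On the spread of start dates, Outcomes sample says: "It is anticipated that at least 500 patients will consent to participation during the first nine months of the study". It also admits patients who joined the clinic before the study started in July 2013.

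On the source of controls, Comparison group(s) speaks of "two different matching algorithms applied to de-identified claims data for non-UAIHC patients". Health Insurance Claims Data says that the health plan receives a coded list of study participants, that only these people are identifiable in the returned file, and that "the remainder of the file will be used to generate the matched control groups".

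**The concern.** The fifth analysis compares the pre/post change in per-member-per-month (PMPM) cost between participants and each of two matched groups. That comparison removes calendar-time effects only if both sides live through the same calendar time. Here a participant who enrolled early or late is matched to someone whose pre and post years are fixed at the group's mean date. A change in plan costs at some calendar date then falls partly into the pre year for one person and into the post year for the other. Both comparison groups inherit the same date rule, so agreement between them would not reveal the problem.

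The second part concerns who is in the pool. If people treated at the clinic can be drawn as controls, the contrast partly compares the clinic with itself and shrinks towards zero.

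**Working it through.** The plan gives no figure for this point, so there is none to reproduce.

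**Inputs.** From the document: 12 months before and 12 after; a July 2013 start; consent over nine months (Outcomes sample). Assumed: uniform entry over W months, with W = 9 from the consent period and W = 12 and 18 as a range. The range is needed because windows run from clinic enrolment, earlier joiners are eligible, and the document does not say how far back they go. (Table 1 words the participants' window as study enrolment; I follow Data Collection and Health Insurance Claims Data, which say clinic enrolment.)

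**Offset and overlap.** Let d be a participant's start minus the mean start. With d uniform on ±W/2, the mean of |d| is W/4.
- W = 9: 2.25 months, at most 4.5. Each 12-month window overlaps the comparators' by 1 − 2.25/12 = 81% on average.
- W = 12: 3 months, 75%. W = 18: 4.5 months, 62%.

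**What cancels in the 12-month totals.** With no true effect:
- Linear trend: post mean minus pre mean is the same for every index date, so bias is 0.
- Stable annual seasonality: every 12-month window averages a full cycle, so bias is 0.
- Equal cost steps every January: a yearly staircase is a linear trend plus an annual cycle, so bias is 0.
- Growth of 6% a year from 400 PMPM (illustrative values): bias about 0.002 on a change of 23.3.

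**What does not cancel.** For a one-off step S at time s relative to the mean date, a person with index d shows a change of S × (1 − |s − d|/12), for |s − d| up to 12.
- Step on the mean date (s = 0), W = 9: comparators show S; participants show S × (1 − 2.25/12) = 0.81 S. The difference is −0.19 S. For W = 12 it is −0.25 S, and for W = 18 it is −0.38 S.
- Step on 1 January 2014, W = 9 from July 2013: the mean start is mid-November 2013, so s = 1.5. Comparators: 1 − 1.5/12 = 0.875. Participants: s − d runs from −3 to 6, so its mean absolute value is (3²/2 + 6²/2)/9 = 2.5, giving 1 − 2.5/12 = 0.792. The difference is about −0.08 S.
- Step 12 months after the mean date, W = 9: comparators show 0; participants show 1.125/12 = 0.09. The difference is +0.09 S.

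The sign therefore depends on when the step falls and on its direction. A cost rise near the mean date looks like savings at the clinic.

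**Monthly model.** The hierarchical model uses up to 12 monthly values on each side. Uniform entry multiplies an annual cosine of amplitude 1 by sin(πW/12)/(πW/12) in participants, while comparators keep amplitude 1. At W = 9 the factor is 0.30, so the largest gap at a mid-month point is (1 − 0.30) × cos 15° = 0.70 × 0.966 = 0.68. At W = 12 the factor is 0 and the gap 0.97. At W = 18 the factor is −0.21 and the gap 1.17. Ordinary seasonality is enough here; no shock is needed.

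**Pool.** One section restricts controls to people who are not patients of the clinic. The other builds the pool by subtracting a list of study participants. Members who did not consent, and consultation-only patients (excluded from the outcomes sample), are not on that list, and no removal step is described. If a share c of the controls received the same care with the same effect, the contrast keeps 1 − c of the effect: 95% at c = 5% and 90% at c = 10%. Both shares are assumptions.

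**The case against.** The strongest reply is that the primary result is the mean pre/post change in totals, and that the usual calendar patterns leave it untouched. That stands. A reader might infer from the date rule alone that the cost contrast is biased, or that yearly benefit changes produce a false effect. The document does not support either reading: equal January steps cancel exactly, and 19% is reached only by a one-off step in the worst position. The seasonal misalignment affects the monthly model, not the totals.

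On the pool, it can be said that the restriction to patients from outside the clinic is the governing rule, and that how it is applied is operational detail that an article may leave to the full protocol. This is fair as far as it goes, so contamination is not shown. But the article does describe how the pool is formed, and that description would not deliver the stated restriction.

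A reader might also infer that pregnancy costs inflate only the controls' post year, because Outcomes sample has "Exclusion criteria: 1) currently pregnant at time of recruitment" and nothing similar is stated for controls. That rests on silence. Controls with an arbitrary date can have deliveries in either year, and participants can have delivered before enrolment or conceive after it. Likewise, a claim that propensity matching would favour clinic members as controls depends on covariates that the article does not list.

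**Conclusion.** The point holds in limited form. The single average date is stated outright and not replaced elsewhere, and it leaves matched people on different calendar windows. For the primary total-cost contrast this opens a route to bias that needs an irregular shock. Under uniform nine-month entry, the error is about 8% of a one-off January 2014 step and at most about 19% of a step on the mean date. The worst case rises to 25% and 38% for 12- and 18-month entry. These figures rest on the assumed entry pattern, and the document does not say whether any such shock occurred. The monthly curves are more exposed.

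The two descriptions of the control pool do not match and need to be reconciled; the effect of any clinic members left in it would be dilution. None of this shows that the cost result will be wrong. It does show that a better rule is available.

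**What to change.** - **Index date.** Give each comparison member the clinic-enrolment date of the participant to whom they are matched, and compute the pre/post windows and the matching covariates as of that date. Calendar-time bias of the kind shown above is then zero by construction, whatever the shape of the trend.
- **Pool.** Before matching, remove anyone with claims from the clinic, or anyone whom the plan flags as a clinic member, and say so in Health Insurance Claims Data so that it agrees with Comparison group(s).
- **Minor.** Where claims codes allow, apply the pregnancy exclusion to controls at their index date.

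The cost is more than programming. The request for non-participants must cover every index date: 24 + 9 = 33 months for nine-month entry, instead of two years, and longer if earlier joiners widen the spread. The file must carry provider identity or a plan flag, which the article does not say it does. The pool becomes slightly smaller. The change is best made before the first claims request goes out, because a two-year extract might not allow the windows to be realigned later.
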